## Abstract

**Background:**

A full-thickness macular hole (FTMH) is a common retinal condition associated with impaired vision. Randomised controlled trials (RCTs) have demonstrated that surgery, by means of pars plana vitrectomy and post-operative intraocular tamponade with gas, is effective for stage 2, 3 and 4 FTMH. Internal limiting membrane (ILM) peeling has been introduced as an additional surgical manoeuvre to increase the success of the surgery; i.e. increase rates of hole closure and visual improvement. However, little robust evidence exists supporting the superiority of ILM peeling compared with no-peeling techniques. The purpose of FILMS (Full-thickness macular hole and Internal Limiting Membrane peeling Study) is to determine whether ILM peeling improves the visual function, the anatomical closure of FTMH, and the quality of life of patients affected by this disorder, and the cost-effectiveness of the surgery.

**Methods/Design:**

Patients with stage 2–3 idiopathic FTMH of less or equal than 18 months duration (based on symptoms reported by the participant) and with a visual acuity ≤ 20/40 in the study eye will be enrolled in this FILMS from eight sites across the UK and Ireland. Participants will be randomised to receive combined cataract surgery (phacoemulsification and intraocular lens implantation) and pars plana vitrectomy with postoperative intraocular tamponade with gas, with or without ILM peeling. The primary outcome is distance visual acuity at 6 months. Secondary outcomes include distance visual acuity at 3 and 24 months, near visual acuity at 3, 6, and 24 months, contrast sensitivity at 6 months, reading speed at 6 months, anatomical closure of the macular hole at each time point (1, 3, 6, and 24 months), health related quality of life (HRQOL) at six months, costs to the health service and the participant, incremental costs per quality adjusted life year (QALY) and adverse events.

**Discussion:**

FILMS will provide high quality evidence on the role of ILM peeling in FTMH surgery.

**Trial registration:**

This trial is registered with Current Controlled Trials ISRCTN number 33175422 and Clinical Trials.gov identifier NCT00286507.

## Background

An idiopathic full-thickness macular hole (FTMH) represents a defect in the area of maximal vision of the retina, the fovea. If left untreated, FTMH usually leads to severe visual impairment, with over a third of patients experiencing a drop in vision to levels of 20/200 or worse [1]. FTMH are common. The incidence has not been reported in the UK but it is estimated to be around 3/10,000/year based on reported incidence in a similar population in the USA [2]. Macular hole surgery represents one of the most common procedures performed by vitreo-retinal surgeons [3].

Four stages (1–4) of FTMH have been described, often with increasing severity of visual loss as the stage of the hole progresses [4]. Around 40% of cases are likely to progress beyond stage 1 [5,6]. Up to 20% of affected people will develop a FTMH in both eyes [7].

Randomised controlled clinical trials conducted in the 1990s showed that surgery was effective for stage 2, 3 and 4 FTMH [8,9]. Several observational studies have suggested that peeling the internal limiting membrane (ILM) of the retina may improve the visual and anatomical success of the surgery (reviewed by Abdelkader and [name]) [10,11]. However, it is difficult to interpret the results of these studies and compare them with those from other series in which the ILM was not peeled since parameters which are likely to influence anatomical and visual outcomes, including stage of the hole, pre-operative vision, duration of symptoms, size of the macular hole, presence of cataract, and extent of ILM peeling varied among study populations.

Some concerns have been raised with regards to the possible damaging effect of ILM peeling in the nerve fibre layer of the retina, which potentially could have adverse effects on central vision [16,17]. There is uncertainty in the literature and among vitreo-retinal surgeons about the balance of potential benefits and adverse effects of ILM peeling in FTMH surgery for stage 2–3 holes. Some surgeons prefer to perform ILM peeling in all cases, whereas others reserve ILM peeling to treat large and/or long-standing macular holes. An Ophthalmology Technology Assessment reviewed the efficacy and safety of macular hole surgery [18] concluded that further research was needed to address whether ILM peeling offered surgical and functional benefit to patients with FTMH.

The hypothesis tested in FILMS is that ILM peeling is superior to the non-peeling procedure with regards to improving vision and quality of life, achieving macular hole closure and that is cost effective.

## Methods and design

### 1. Trial recruitment

Participants will be identified in general and specialised ophthalmic clinics of all eight hospitals participating in this trial: Aberdeen and Dundee (Scotland); Bristol, Sunderland, Oxford, Liverpool, (England); Dublin and Waterford (Ireland).

#### 1.1. Inclusion and exclusion criteria

Eligible participants are those with idiopathic FTMH in stages 2–3, of less or equal than 18 months duration (based on symptoms reported by the patient) and with a visual acuity equal to or worse than 20/40 in the study eye. If bilateral idiopathic FTMH are present, the eye with most recent onset of visual loss will be randomised for the study. Individuals with FTMH in stages 1 and 4, those with idiopathic FTMH stages 2–3 but longer than 18 months duration or with other causes of decreased vision (e.g. corneal scarring, age-related macular degeneration, diabetic retinopathy, glaucoma if central and/or paracentral absolute visual field defects are present) and those with FTMH related to high myopia (> 6 dioptres) or trauma will be excluded from the study. Individuals that do not understand English and those unable to give informed consent will not be included.

#### 1.2. Informing potential participants about the trial

The local clinical investigator (consultant vitreo-retinal surgeon or a doctor/nurse/optometrist working with the consultant) will describe the study face-to-face to potentially eligible participants. Verbal information will be supported by a patient information leaflet containing information about macular holes and current surgical treatments.

#### 1.3. Consent to participate

Once eligibility has been confirmed, the local clinical investigator will ask if the potential participant is interested in joining the trial. If so, the participant will be given a consent form. After checking with the participant that the consent form is understood, the consultant vitreo-retinal surgeon will invite the participant to sign the form and will countersign it. One copy of the consent form will be given to the patient, another will be filed in the hospital case notes, and the third will be kept at the Trial Office (Centre for Healthcare Randomised Trials (CHaRT), Health Services Research Unit, University of Aberdeen, Scotland).

#### 1.4 Information collected at trial entry

Once a participant agrees to join the trial, research optometrists and vitreo-retinal surgeons at each centre will record baseline data on FILMS case report forms (CRF) including full name, address and telephone number, date of birth, gender, hospital number and general practitioner's contact details, and check that eligibility criteria are met prior to enrolment on the study. CRFs are contained in booklets (one booklet per participant recruited), with triplicates of each visit CRF (one to keep in the booklet, one to file in the patient's medical records and one to be sent to the Trial Office) with the exception of the surgical CRF (see below) for which there are only two copies (one for the surgeon and one to be sent by the surgeon to the Trial Office to maintain masking of the participant and optometrist) in each booklet. Some demographic data (gender), the date of attempted recruitment, the centre, and the grounds for non-inclusion will be collected also on ineligible and unwilling participants as well as on participants not recruited for other reasons.

Within 2 weeks (± 2 weeks) prior to the date scheduled for the surgery baseline data on primary and secondary outcomes studied (Table 1) will be collected and recorded on the appropriate CRF for each participant. In addition, information on duration of symptoms related to the macular hole and lens status (phakic, pseudophakic or aphakic) and lens grading in phakic eyes, based on the Age Related Eye Disease Study (AREDS) classification, will be also collected [19].

**Table 1 T1:** Summary of outcome measures, tools used to obtain them, and eye in which they were assessed at baseline and at each follow-up visit

**Outcome measure**	**Tool**	**Eye**	**Baseline**	**1 month**	**3 months**	**6 months**	**24 months**
Distance VA	ETDRS charts	Study eye Contralateral eye	X X		X X	X X	X X

Near VA	Bailey-Lovie charts	Study eye Contralateral eye	X X		X X	X X	X X

Contrast sensitivity	Pelli-Robson chart	Study eye Contralateral eye	X X			X X	

Reading speed	MN Read chart	Study eye Contralateral eye	X X			X X	

Stage of FTMH^•^	Slit-lamp biomicroscopy	Study eye	X				

Status of FTMH	Slit-lamp biomicroscopy^+^ Colour and red free photographs^#^	Study eye Study eye	X X	X X	X X	X X	X X

HRQoL	NEI-VFQ-25 and EQ-5D questionnaires	N/A	X			X	X

Costs:							
- Primary care	Health Service Utilisation questionnaire	N/A				X	
- Secondary care	Targeted questions in CRF	N/A			X	X	X
- Participants	Participant Unit Cost questionnaire	N/A				X	

VA = visual acuity; ETDRS = Early Treatment Diabetic Retinopathy Study visual acuity charts; FTMH = full-thickness macular hole; HRQoL = health related quality of life; N/A = not applicable; ^• ^= Stage 2: absence of posterior vitreous detachment and whenever the largest diameter of the hole is ≤ 400 microns; Stage 3: absence of posterior hyaloid separation but when the largest diameter of the hole is > 400 microns, as classified by the vitreo-retinal surgeon; ^+ ^= closed, open with subretinal fluid around it or open with no subretinal fluid around it as determined by the vitreo-retinal surgeon; ^# ^= size of the macular hole and status of the macular hole (closed, open with subretinal fluid around it or open with no subretinal fluid around it) as determined by a masked observer at the University of Aberdeen.

### 2. Trial interventions

All surgeries will be performed by a consultant vitreo-retinal surgeon or by an experienced vitreo-retinal fellow, supervised by the consultant vitreo-retinal surgeon. All phakic participants will undergo cataract extraction by means of phacoemulsification and intraocular lens implantation at the time of the macular hole surgery.

Participants will be randomised to receive macular hole surgery either with ILM peeling or without ILM peeling. In participants not receiving ILM peeling, a pars plana vitrectomy will be performed, including detachment and removal of the posterior hyaloid, followed by a fluid-air exchange and air-gas (12% C_3_F_8_) exchange. In participants undergoing ILM peeling, a pars plana vitrectomy, including detachment and removal of the posterior hyaloid, will be similarly performed but, in addition, following ILM staining with Trypan blue (Membrane Blue, DORC) the ILM will be peeled off the retina, in an area of around 1–2 disc diameters around the hole. If staining of the ILM is considered inadequate, re-staining is permitted. The surgery will be completed by a fluid-air exchange and an air-gas (12% C_3_F_8_) exchange. Details of the surgery will be recorded in the appropriate case report form. To assure masking of the optometrists and participants (see below) to the allocated treatment, once the CRF for the surgery is filled one copy will be removed from the CRF booklet and kept locked by the vitreo-retinal surgeon and the other will be sent immediately to the Trials Office.

The surgical CRF contains information on date of admission; grade of the surgeon, assistant surgeon and anaesthetist [consultant, staff grade or associate specialist (non-training posts) or registrar or senior house officer (training posts)]; type of anaesthesia; performance or lack of performance of ILM peeling around the hole and the degree of completeness of this manoeuvre (peel complete or incomplete); confirmation that the vitreous was attached at the time of the surgery and any complications occurring intraoperatively. In addition, the time at which the participant enters the anaesthetic room, the "operating time", defined as the time between starting the case (getting the operating microscope over the participants' eye, ready for the surgery) and completing the case (moving the microscope away from the participant's eye at the end of the procedure), and the time at which the participant leaves the theatre (or the recovery room when appropriate) will be recorded. The date of discharge from the hospital will also be recorded.

All participants will be instructed to posture face down as soon as possible after the surgery for 45 minutes every hour for a period of 5–7 days. Each participant will be given a posturing chart to record the time postured during these 5–7 days, which will be sent, once filled, to the central Trials office in Aberdeen. In addition, at the 1 month follow-up visit the participant will be asked how many days in total did they posture following surgery (in case they have not completed and returned the posturing chart).

### 3. Treatment allocation

The existing central randomisation service (fully automated telephone randomisation) in the Centre for Healthcare Randomised Trials (CHaRT), Health Services Research Unit at the University of Aberdeen, will be used to randomise participants. A minimisation algorithm (according to Taves, with p = 1)^20^, considering trial centre, distance visual acuity in the study eye and in the fellow eye (20/40–20/160; 20/200–20/500; <20/500), duration of the macular hole (= 1 year; > 1 year), lens status (phakic;aphakic;pseudophakic) and stage of the hole (Grade 2; Grade 3), as classified by the vitreo-retinal surgeon will be used.

### 4. Masking of intervention and outcome assessment

Patients, optometrists obtaining data on visual function, photographers and the observer at the University of Aberdeen responsible for analysing the size and status of the hole will be masked with regards to the type of procedure performed to the participant and will remain masked throughout the study. Only the vitreo-retinal surgeon, for obvious reason, will not be masked to the type of surgery performed.

At enrolment potential participants will be informed that they will be unaware as to whether they had received internal limiting membrane peeling at the time of the macular hole surgery. The surgeons will know which type of procedure they have performed but they will not reveal this to participants. The only scenario in which the participant will be unmasked is if the macular hole is not closed following surgery. In this situation, the participant will be offered further surgery and the nature of this surgery will be discussed with the participant.

### 5. Subsequent arrangements

#### 5. 1. Informing the general practitioner

Following formal trial entry, the sites will contact the general practitioner through the post to let him/her know about the participant's involvement in the trial. The letter sent to the general practitioner includes a brief description of the trial together with a request to notify the Trial Office if any events that may lead to their patient failing to attend any of the follow-up visits.

#### 5. 2. Follow-up

Participants will be followed at 1, 3, 6 and 24 months post surgery. Visits will take place within 2 weeks from the scheduled date. All data will be recorded at each visit in the appropriate CRF. Table 1 summarises the data collected at each of the follow-up visits. Post-operative complications will also be recorded at each visit.

### 6. Data processing

Data from the various sources outlined above will be sent to the Trial Office in Aberdeen for processing. A random 10% sample of that data will be double checked for accuracy. Staff in Aberdeen will work closely with investigators at all participating sites to ensure complete and accurate data recording. Extensive range checks will be conducted to further enhance the quality of the data.

### 7. Outcome assessment

The primary outcome of the study is the mean difference between treatment groups in the Early Treatment Diabetic Retinopathy Study (ETDRS) distance visual acuity score at 6 months.

Secondary outcomes include ETDRS distance visual acuity at 3 and 24 months, near visual acuity at 3, 6 and 24 months, contrast sensitivity at 6 months, reading speed at 6 months, anatomical closure of the macular hole at each time point (1, 3, 6 and 24 months), health related quality of life (HRQOL) at 6 months, costs to the health service and the participant, incremental costs per QALY and adverse events.

A summary of the outcome measures studied and the tools used for their assessment at baseline and at each follow-up visit is provided in Table 1.

### 8. Analysis of the data

#### 8.1. Statistical analysis

The principal analysis will take place when six month data collection is complete. A subsequent analysis will be conducted once 24 months data is available. The statistical analysis will be based on all patients as randomised, irrespective of subsequent treatment received and, thus, will follow the intention to treat principle. Additionally, the primary analysis will be based upon available case data with no imputation of missing values. Sensitivity analyses, which impute extreme values will be performed for the primary outcome (visual acuity at 6 months) and for other visual function and quality of life secondary outcomes as appropriate. Statistical significance for the primary and secondary outcomes will be based on two-sided tests with 2P ≤ 0.05 taken as the criterion for statistical significance. The primary outcome of ETDRS visual acuity score at 6 months will be compared between the two groups (ILM peel and no ILM peel) using a generalised linear model to calculate the mean difference adjusted for the baseline score and minimisation covariates. The primary outcome will additionally be analysed according to the pre-specified subgroups (see Treatment Allocation section, minimisation criteria, above) by including corresponding interaction term(s) in the regression model. For these subgroup analyses, stricter criteria for statistical significance (2P ≤ 0.01) will be applied. Secondary outcomes, adverse events and re-operation rates will be analysed using generalised linear model with adjustment for minimisation covariates as appropriate. Analyses of health related quality of life measures (EQ-5D and VFQ-25) and secondary measures of visual function (contrast sensitivity, MN Reading speed and distance and near visual acuity) will be adjusted for the corresponding baseline score in addition to the minimisation variables.

#### 8.4 Economic analysis

##### 8.4.1 Estimation of costs

Costs that fall on both the participant and the health service will be elicited. Participant costs will comprise three main elements: self purchased healthcare; travel costs for making return visit(s) to NHS health care; and time costs of travelling and attending NHS health care.

Self-purchased health care will include items such as prescription costs and over the counter medications. Information about these will be collected in the Participant Unit Cost questionnaire, which will be sent by post to each participant prior to the 6-month visit, and which will be returned, once filled by the participant, to the central office in Aberdeen. Estimation of travel costs requires information from participants about the number of visits to their general practitioner, ophthalmologist or optometrists and the unit cost of making a return journey to each type of health care provider. The cost of participant time will be estimated in a similar manner. The participant will be asked, in the Participant Unit Cost Questionnaire, how long they spent travelling to and attending their last visit to each type of health care provider. Participants will be asked also what activity they would have been undertaking (e.g. paid work, leisure, housework) had they not attended the health care provider. These data will be presented in their natural units, e.g. hours, and also costed using standard economic conventions, e.g. the Department of Transport estimates for the value of leisure time. These unit time costs, measured in terms of their natural and monetary terms, will then be combined with estimates of number of health care contacts derived from the health care utilisation questions.

Health service costs of surgery will be recorded prospectively for every participant in the study. Main areas of costs are operation costs include staff, consumables, capital and overheads.

Use of secondary care services following the operation will be collected on the 3, 6 and 24 month CRFs. Information on non-protocol (protocol visits are those scheduled for the purposes of data collection) eye-related visit(s) to the outpatients/casualty department or hospital admission(s) and need for further surgery(ies) will be also collected.

Use of primary care services such as prescription medications, contacts with primary care practitioners e.g. general practitioners, practice nurses, optometrists and ophthalmologists will be collected via the Health Care Unit Cost questionnaire administered at 6 months follow-up.

##### 8.4.2 Estimation of effectiveness

In the economic analysis effectiveness at 6 and 24 months will be measured in terms of quality adjusted life years (QALYs). QALYs will be estimated by the participants' responses to the EQ-5D questionnaire (administered at baseline, 6 and 24 months). The estimation of QALYs will take account of the mortality of study participants. Participants who die within the study follow-up will be assigned a zero utility weight from their death until the end of the study follow up. QALYs before death will be estimated using linear extrapolation between the QALY scores at baseline and all available EQ-5D scores up to death or the end of the study follow-up. The method of eliciting QALYs described is one commonly adopted in economic evaluation [21].

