##### 8.4.3 Estimation of cost-effectiveness

The primary analysis will be based on six-month follow-up of the trial for the incremental cost per QALY. A second analysis will be conducted for a 24-month time horizon using the same methods as outlined in this manuscript. The results will be presented as point estimates of mean incremental costs, QALYs, and incremental cost per QALY. Measures of variance for these outcomes are likely to involve bootstrapping estimates of costs, QALYs, and incremental cost per QALY. Incremental cost-effectiveness data will be presented in terms of cost-effectiveness acceptability curves (CEACs).

Other forms of uncertainty, e.g. concerning the unit cost of a resource from the different centres, will be addressed using standard deterministic sensitivity analysis. Where feasible the results of the sensitivity analyses will also be presented as CEACs.

A secondary economic analysis will be presented. In this analysis the costs and consequences measured in terms of visual function and adverse events will be presented as a cost-consequence analysis. Where appropriate uncertainty will be explored using similar approaches to those outlines above.

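### The primary six-month QALY uses EQ-5D at baseline and 6 months only, so speed of recovery and losses that resolve before month 6 do not enter it, although further surgery is recorded for costing

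*Protocol article*

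**What the plan says.** All references are to the protocol article.

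- **Utility measurement.** Section 8.4.2 bases QALYs on the "EQ-5D questionnaire (administered at baseline, 6 and 24 months"). Table 1 (section 1.4) agrees: the row for the "NEI-VFQ-25 and EQ-5D questionnaires" is marked at baseline, 6 and 24 months and blank at 1 and 3 months.
- **Visits.** Section 5.2: "Participants will be followed at 1, 3, 6 and 24 months post surgery". Two visits therefore fall inside the first six months without an EQ-5D.
- **Horizon.** Section 8.4.3: "The primary analysis will be based on six-month follow-up of the trial for the incremental cost per QALY". A 24-month analysis by the same methods follows.
- **Joining the scores.** Section 8.4.2: "QALYs before death will be estimated using linear extrapolation between the QALY scores at baseline and all available EQ-5D scores". Between observed scores this is linear interpolation. Utility is set to zero after death.
- **Re-operation.** Section 4, on a hole that has not closed: "In this situation, the participant will be offered further surgery". Section 8.1 plans a between-arm comparison of re-operation rates.
- **Costs.** Section 8.4.1 takes secondary care use from the 3, 6 and 24 month forms, and adds that "need for further surgery(ies) will be also collected".

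**The concern.** The two halves of the cost-effectiveness ratio are observed differently over the same six months. Resource use, including further surgery, is recorded during the interval. Utility is recorded only at its two ends.

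Whatever happens equally in both arms cancels from the incremental QALY. What follows from failed closure need not cancel. The trial's hypothesis is that peeling achieves closure more often, and the Background describes two earlier randomised trials that found higher closure with peeling. Failed closure leads to an offer of further surgery. The plan therefore anticipates a possible arm difference in an event whose interim health effect its primary QALY may not register. At stake is the denominator of the primary economic result.

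**Working it through.** The plan states no utility, QALY, re-operation rate or re-operation timing, so it has no figure of its own to reproduce here. Only step 1 follows from the documents alone. Every utility, rate and duration below is an assumption.

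**1. What the plan fixes.** For a survivor with scores u0 at baseline and u6 at month 6, over half a year:

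QALY = 0.5 × (u0 + u6)/2 = 0.25 × (u0 + u6)

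No other quantity enters.

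**2. Different courses with the same QALY.** Assume u0 = 0.75 and u6 = 0.80. The plan gives 0.25 × 1.55 = 0.3875 in every case. With EQ-5D also at months 1 and 3, the trapezoids span 1, 2 and 3 months:

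| Course | Scores at 0, 1, 3, 6 months | Area under the curve |
|---|---|---|
| Early recovery | 0.75, 0.75, 0.80, 0.80 | 0.0625 + 0.1292 + 0.2000 = 0.3917 |
| Hole still open at month 3 | 0.75, 0.75, 0.75, 0.80 | 0.0625 + 0.1250 + 0.1938 = 0.3813 |
| Re-operation dip at month 3 | 0.75, 0.75, 0.65, 0.80 | 0.0625 + 0.1167 + 0.1813 = 0.3604 |

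**3. A dip that resolves before month 6.** Missed between-arm difference = difference in re-operation rate × utility loss × weeks/52:

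- low: 0.1 × 0.1 × 4/52 = 0.0008 QALY
- middle: 0.2 × 0.1 × 8/52 = 0.0031 QALY
- high: 0.3 × 0.2 × 8/52 = 0.0092 QALY

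For scale, a between-arm utility difference of 0.03 at month 6 is worth 0.25 × 0.03 = 0.0075 QALY on the plan's line, and one of 0.05 is worth 0.0125.

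**4. Delayed recovery.** Assume a gain of 0.05, reached two months after a successful operation.

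- Closed at first surgery: 0.05 × (6 − 2)/12 = 0.0167 QALY.
- Re-operated at month 3: 0.05 × (6 − 5)/12 = 0.0042 QALY.
- Difference: 0.0125 QALY per re-operated participant.

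The plan credits both with 0.25 × 0.05 = 0.0125, a difference of zero.

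**5. A dip still present at month 6.** A loss of 0.10 lasting four weeks truly costs 0.10 × 4/52 = 0.0077 QALY. If it is present at the month-6 visit, the plan charges 0.25 × 0.10 = 0.025. Here the error runs the other way.

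**6. Whether another part of the plan recovers this.** The 24-month analysis adds one later score and leaves the first six months as they are. The deterministic sensitivity analysis in section 8.4.3 gives unit costs as its example. The cost-consequence analysis sets visual function and adverse events beside costs but does not alter the QALY. A later analysis plan cannot restore utilities that were never measured.

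**The case against.** The strongest reply is that section 8.4.2 calls its method a common one, nothing in it contradicts another section, and more EQ-5D points are a matter of preference. The consequences of re-operation are also visible elsewhere: re-operation rates are compared between arms, and acuity and hole status are measured at 3 months. This stands as a reason to call the point an improvement and not an error. It does not supply the missing part of the QALY.

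Four stronger readings are tempting, and the documents do not support them.

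- **That re-operation is costed in full while its health effect is ignored.** Section 8.4.1 says that the need for further surgery is collected. It does not say how a re-operation is valued.
- **That any loss in between is set to zero.** A hole still open at month 6, or recovery still incomplete then, lowers u6 and is charged across the half-year. Only loss that has resolved by that visit disappears.
- **That the result is biased against the better-closing arm, without condition.** Step 5 shows the opposite case. Section 4 says only that "the participant will be offered further surgery", with no rate, uptake or timing.
- **That the omission is 10–120% of the effect.** Those figures are 0.0008/0.0075 and 0.0092/0.0075, and every input is assumed. Against the 0.0125 comparator the same inputs give about 6% to 74%. The low end is about 0.3 of a day in full health (0.0008 × 365).

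The remedy is also imperfect. With scores at 0, 1, 3 and 6 months, the month-3 score carries 2.5 months of weight, so a 0.10 dip caught there is charged 0.10 × 2.5/12 = 0.0208 QALY, against 0.0077 for a true four-week loss. With month 3 alone added, the weight is 3 months and the charge 0.025. A short dip between visits is still missed. The gain lies mainly in seeing holes that remain open and recovery that comes late.

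**Conclusion.** The point holds as a limitation of the design. Within the primary horizon the QALY is a two-point line, so it cannot register differences in speed of recovery, or losses from an open hole or re-operation that resolve before month 6. Further surgery in the same months is recorded for costing. Losses still present at month 6 may be overstated.

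If peeling changes first-operation closure, the incremental QALY can be distorted. It is understated for the better-closing arm on the condition that the losses resolve before month 6. Neither the net direction nor the size can be settled from the documents. The range of 0.0008 to 0.009 QALY assumes a 10–30 point difference in re-operation rates and a utility loss of 0.1–0.2 for 4–8 weeks, and at its low end it may be negligible. This is an inexpensive improvement of low severity, not a fault that invalidates the economic analysis.

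**What to change.** Add the EQ-5D to the existing 3-month visit, where secondary care use is already recorded, and preferably to the 1-month visit as well. Mark the added time points in Table 1 and in section 8.4.2, and state that the QALY is the area under the curve through all available scores. Section 8.4.2 already refers to all available EQ-5D scores, so the method itself does not change.

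The cost is one short questionnaire at visits that take place anyway, an amendment to the case report form, a small participant burden and some extra missing items. No new visit is needed. Short dips between visits would still be captured imperfectly.
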